## **EXECUTIVE SUMMARY**

Abstract of thesis presented to the Senate of Universiti Putra Malaysia in fulfilment of the requirement for the degree of Doctor of Public Health

**[name]**

**May 2022**

**Chair : [name] [name]**  
**Faculty : Faculty of Medicine and Health Sciences**

### **Introduction:**

The food and beverages industry contributed a significant income to Malaysia's Gross Domestic Products (GDP). The contribution is projected to swell more in the upcoming years. As the industry expands, the demand for the workforce in the food premises will also continuously increase. The workforce substantially involves workers from the food processing sector, food distribution sector, and food service sector in the food premises. Regardless of the section, it is essential for food handlers who work in food premises to be equipped with the proper knowledge, attitude, and practice (KAP) towards safety and health. This is because they are exposed to risks arising from physical, chemical, biological, mechanical, and social hazards while performing their duties like in any other occupation. Therefore, a well-trained food handler equipped with the right KAP for safety and health will contribute to a safer and positive working environment, smoother work operation, better services, reduced accidents at the workplace, and subsequently increased workers' motivation and productivity.

### **Objective:**

The general objective of this study is to develop, implement, and evaluate the effectiveness of the occupational safety and health training program in increasing the KAP among food handlers.

**Methodology:**

The study is a single-blinded, cluster randomized controlled trial study, expected to be conducted from 1st December 2023 to 30th November 2024 among 139 registered food handlers in Selangor under municipal in the working-age between 18-65 years old. The respondents will be allocated into intervention and control group. The intervention group will receive TRIMOSH intervention while the control group will receive standard training. The data will be collected via self-administered questionnaires and has been analyzed using SPSS version 25.

**Result:**

A total of 139 participants expected to be finally selected to participate in the study with response rate of more than 80%. At baseline, the characteristics of the sociodemographic, socioeconomic, working experience and training attendance of food handlers hypothesized to show no difference in between group. It is hypothesized that there will be a significant improvement on knowledge, attitude and practice (KAP) on occupational safety and health at food premises among food handlers in the intervention group compared to the control post training and 1 month follow up. In the GLMM analysis, it is hypothesized that the TRIM-OSH is associated with improving KAP among food handlers on occupational safety and health at food premises.

**Conclusion:**

In order to achieve the desired outcome, there is a role of structured training. Thus, a theory-based intervention module on occupational safety and health at food premises (TRIM-OSH) to improve KAP on occupational safety and health among food handlers will be developed and examined through an intervention study. In this study, the participants will be randomly selected and subsequently assessed for their KAP pre and post-participation in the module. In addition, the study will assess the module's effectiveness in improving KAP of occupational safety and health among the targeted population in Selangor, through statistical analysis, with the aim of national implementation in the future.

## CHAPTER 1

### INTRODUCTION

#### 1.1 BACKGROUND

##### 1.1.1 Industry Overview

The food and beverages industry contributed a significant income to Malaysia's Gross Domestic Products (GDP). Its contribution is projected to swell more in the upcoming years. The food and beverages industry can be divided into three main sections: food processing, food distribution, and food services. Food processing sectors mainly involve edible products and preparations such as poultry, seafood, cereal, etc. The food distribution sector refers to the supply and distribution of local-produced and imported products to the end-user through small-scale retailers such as local grocery stores or large-scale retailers such as Tesco, Jaya Grocer, AEON Big, etc. Food service sector includes those businesses involved with fine dining restaurants, international chains, hotel, pub, bars, cafes, and stalls businesses.

The Malaysian Investment Development Authority (MIDA) data shows that the food-processing sector alone accounts for about 10% of Malaysia's manufacturing output. Processed food contributed about RM21.76 billion and is exported to more than 200 countries, while the import value of processed food amounted to RM20.27 billion in 2019. The agency also estimated that the annual growth rate of the Food and Beverages industry stands at 7.6% in 2019. (MIDA, 2019). In 2017, Malaysia's food distribution sectors value was estimated at RM20.48 billion (FIT, 2020). In a similar year, the food services sector's gross output in Malaysia was valued at RM82.8 billion, as reported by the Department of Statistics Malaysia (DOSM) in their report (DOSM, 2019). The Covid-19 pandemic has undoubtedly dampened the growth of the food industry in the current year; however, the economic situation is expected to recover as the pandemic settles down.

Based on the data by Economic Planning Unit, Prime Minister's Department (EPU), the vast number of workforces in the food and beverages industry can be found under class C (Manufacturing industry), class G (Wholesale and retail trade, repair of motor vehicles and motorcycles) and class I (Accommodation and food service activities). The numbers of employed persons in all mentioned classes of Industry show a consistently increasing trend from year to year since 2010 till the year the Covid-19 crisis sets in. In 2019, the number of employed persons in class C was estimated at 2.7 million, class G at 2.6 million, and class I at 1.5 million, which comprised up to 45% of employment in comparison with other industries such as class A (Agriculture, forestry, and fishing), class F (Construction), class P (Education) and, etc. (EPU, 2019).

As the Covid-19 pandemic crisis became pandemic, the economy recovered, and the industry expanded, the demand for the workforce in the food and beverages industry at food premises is expected to increase. Food premises are the premises used for or in connection with the preparation, preservation, packaging, storage, conveyance, distribution, or sale of any food or the relabelling, reprocessing, or reconditioning of any food (Laws of Malaysia Act 281 Food Act, 2006). As the workers' volume increases, the number of accidental injuries or occupational diseases related to the food and beverages industry is expected.

### **1.1.2 Injuries and illnesses in the Industry**

As in any other profession, an individual who works in food premises will be exposed to various hazards related to the nature of their work. Failure to ensure occupational safety and health at food premises may lead to accidental injury, or occupational diseases that are not only detrimental to the food handler's general well-being but also affect the productivity of the organization as the affected workers or employees may have to stay days away, restricted, or transferred (DART) from work.

Based on the Bureau of Labor Statistics data, United States Department of Labor (BLS), the highest number of nonfatal occupational injuries and illnesses involving days away from work (DAFW) in private Industry in 2020 goes to those who involve in health care and social assistance. The observation was tallied with the Covid-19 pandemic situation and contributed to about 30.4% of total reported cases of 1.18 million. It is followed by manufacturing (14.1%), retail trade (12.8%), transportation and warehousing (7.8%), and accommodation and food services (7.2%). The mentioned industries already contributed more than 70% of the reported cases (U.S. DOL, BLS (a), 2020). However, the number of food handlers working at food premises in this data can be found in the manufacturing, retail trade, accommodation, and food services sector. In a further analysis based on occupation, the highest number of nonfatal occupational injuries and illnesses involving days away from work (DAFW) in private Industry involving food handlers within the industries contribute about 22% of total reported cases or around 0.3 million cases (U.S. DOL, BLS (b), 2020).

Of all the reported injuries and illnesses cases, cuts, lacerations and punctures (15%) was the highest contributors of injuries and illnesses for known classified cases among food handlers, followed by sprain, strains, and tears (15%), soreness and pain (13%), thermal burn (8%), bruises and contusions (5%), fractures (4%), multiple traumatic injuries (1%), chemical burns and corruptions (1%), carpal tunnel syndrome (1%), amputation (0.4%) and tendonitis (0.06%). However, there was a sum of reported cases that were non-classifiable and contributed to about 35% of the total reported cases among food handlers (U.S. DOL, BLS (c), 2020). The highest number of injuries and illnesses experienced by food handlers have resulted from exposure to harmful substances or environments (34%), followed by contact with objects or equipment (22%), falls, slips, and trips (21%), overexertion and bodily reaction (19%), transportation incidents (2%), violence and other injuries by persons or animal (1%), other events or exposures (0.4%) and fires and explosions (0.09%) (U.S. DOL, BLS (d), 2020).

From the similar data, the top ten occupations that have been reported to have the highest incidence of occupational injuries and illnesses among food handlers were observed among those who work in food preparation and serving related occupations (25%), cooks, and food preparation workers (10%), food and beverage serving workers (9%), food processing workers (6%), cooks (5%) fast food and counter workers (5%), food preparation workers (5%), supervisors of food preparation and serving workers (4%) butchers and other meat, poultry and fish processing workers (3%) and other food preparation and serving related workers (3%) (U.S. DOL, BLS (c), 2020).

## **1.2 PROBLEM STATEMENT**

Since 1996, the Ministry of Health Malaysia (MOH) has launched the food handler training course to give exposure and awareness to food handlers on food safety, hygiene, self-hygiene, and premise hygiene, mainly to prevent food poisoning incidents in the country. Subsequently, under Food Hygiene Regulations 2009, all food handlers are compulsory to attend the Food Handler Training Programme organized by any school or institute that has been certified by MOH. Food handlers are defined as individuals who are (1) directly involved in the food preparation, (2) come into contact with food or food contact surfaces, and (3) handle packaged or unpackaged food, or appliances, on any food premises (Laws of Malaysia Act 281 Food Act, 2006). Under this regulation, any food handler who fails to undergo training or obtain a Certificate of Food Handlers Training shall be liable to a fine or compound not exceeding RM10,000 or imprisonment for a term not exceeding 2 years (Food Hygiene Regulation, 2009).

The food handler training module by MOH has been formalized and uniformed and comprises four sections: introduction, food hygiene, food safety, and critical factors of food poisoning (MOH, 2014). However, despite this module being compulsory, the data reported by the Department of Occupational Safety and Health (DOSH)

shows that the number of cases reported and cases confirmed for occupational poisoning and disease generally show a consistently increasing trend from 2010 to 2019.

Regarding occupational safety and health of workers who work as food handlers in Malaysia, they are generally governed and regulated by Act 514 Occupational Safety and Health (OSHA) Act 1994 as for any other occupations. It is within the spirit of the act to secure the safety, health, and welfare of persons at work to protect the workers and others from any risk or health implication associated with the activities of persons at work and prevent occupational diseases. An occupational disease is defined as any disease contracted due to exposure to risk factors arising from work activity (DOSH, 2021). However, there is currently no occupational safety and health training module, required or made compulsory by the government for food handlers to equip them with appropriate knowledge, attitude, and practice on occupational safety and health to prevent injuries and illnesses related to their work.

Based on local statistics, the manufacturing industry, including the food and beverages sector, accounted for the most significant contributor to all confirmed occupational poisoning and disease cases at 82.3% (6792). On the other hand, the number of confirmed cases from hotels and restaurants and wholesale and retail trades accounted for 0.5% (41) and 0.3% (25) of total confirmed cases. According to the sector, in terms of accidental injury at the workplace, DOSH Malaysia generally reported an increasing trend of accidents among workers from year to year. In 2020 only, 62% (4202) of accidents with temporary disability, 84% (231) of accidents with a permanent disability, and 34% (73) of death reported to DOSH were coming from the manufacturing industry. On the other hand, 2% (137) of accidents with temporary disability, 0.4% (1) of accidents with a permanent disability, and 0.7% (2) of death reported to DOSH came from the hotel and restaurants industry. Wholesale and retail trade reported a 2% (126) of accidents

with temporary disability, 0.4% (1) of accidents with a permanent disability, and 0.4% (1) of death to DOSH.

Based on the available data on occupational poisoning, occupational diseases, and accidents that lead to temporary and permanent disability among workers, especially in the food and beverages industry, related training is appropriate for food handlers to prevent such occurrences.

### **1.3 SIGNIFICANCE OF STUDY**

The study will be able to provide a more in-depth understanding to the researcher, educator, and trainer who are involved in the food industry on the issue of occupational safety and health among food handlers and able to help them in identifying the training content that is suitable, related and appropriate to the food industry trainee.

The analysis of this study will allow the researcher to identify the effectiveness of the developed theory-based intervention module on occupational safety and health at food premises (TRIM-OSH) in improving KAP on the occupational safety and health among the food handlers working on food premises. It will also be able to guide the researcher on the feasibility of this program on a larger scale, e.g., state or national level.

A practical theory-based intervention module on occupational safety and health at food premises (TRIM-OSH) may help the government add value to the current food handler training program by including the occupational safety and health component to prevent occupational-related poisoning, diseases, and accidents at food premises.

## **1.4 RESEARCH QUESTION**

Why should this occupational safety and health training program be done among food handlers? Is there any deficiency tied to the need?

Are this occupational safety and health training program effective in increasing the knowledge, attitude, and practice among food handlers regarding occupational safety and health at work?

## **1.5 RESEARCH OBJECTIVE**

### **1.5.1 GENERAL OBJECTIVE**

The general objective of this study is to develop, implement, and evaluate the effectiveness of the occupational safety and health training program in increasing the KAP among food handlers.

### **1.5.2 SPECIFIC OBJECTIVE**

The specific objectives of this study are:

1. To describe the baseline sociodemographic, socioeconomic, working experience, training attendance, and means KAP score of food handlers.
2. To develop and implement a theory-based intervention module for food handlers in Selangor, Malaysia.
3. To evaluate the effectiveness of the SCT constructs as the main framework of the intervention module in improving KAP among food handlers between the intervention and control group.

4. To describe and compare the effectiveness of the TRIM-OSH on the change of knowledge, attitude and practice compared to standard training among food handlers between and within groups at the end, and one-month post training, after controlling for covariates.

## 1.6 RESEARCH HYPOTHESIS

The research hypothesis of this study is:

- H1:** The sociodemographic, socioeconomic, working experience, and training attendance characteristics of the intervention and control groups would be the same.
- H01:** There is no significant differences in the sociodemographic, socioeconomic, working experience, and training attendance characteristics of the intervention and control groups.
- H2:** The KAP on occupational safety and health at food premises of the intervention and control groups at the baseline would be the same.
- H02:** There is no significant differences in the KAP on occupational safety and health at food premises of the intervention and control groups at the baseline.
- H3:** The SCT constructs as the main framework of the intervention module is effective in improving KAP among food handlers between the intervention and control group.
- H03:** The SCT constructs as the main framework of the intervention module have no significant effect in KAP among food handlers between the intervention and control group.
- H4:** The TRIM-OSH effectively improves KAP on occupational safety and health at food premises among food handlers.

**H04:** There is no significant differences in the KAP on occupational safety and health at food premises of the intervention and control groups at post-intervention.

## CHAPTER 2

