All results of log-transformed data considered underlying data transformation in result interpretation. The confidence interval will be set at 95% for mean estimations. The level of significance, alpha ( $\alpha$ ), will be set at 0.05. A p-value of less than 0.05 pertained to the decision rule. The dependent variables measured in this study are the outcome (primary and secondary) and effectiveness of the SCT constructs as the base of theory-based intervention module in occupational safety and health training among food handlers.

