## RESULTS

## 4.1 Results Dummy Table

Table A. Baseline comparison of sociodemographic, socioeconomic, working experience, and training attendance characteristics between-group (n=).

|                                       | Group median (IQR) / n (%) |              | Statistical Test | p-value |
|---------------------------------------|----------------------------|--------------|------------------|---------|
|                                       | Control                    | Intervention |                  |         |
| Age (years)                    |                            |              |                  |         |
| Gender                         |                            |              |                  |         |
| Male                                  |                            |              |                  |         |
| Female                                |                            |              |                  |         |
| Ethnicity                      |                            |              |                  |         |
| Malay                                 |                            |              |                  |         |
| Chinese                               |                            |              |                  |         |
| Indian                                |                            |              |                  |         |
| Others                                |                            |              |                  |         |
| Educational status             |                            |              |                  |         |
| Primary school                        |                            |              |                  |         |
| Secondary school                      |                            |              |                  |         |
| SPM/STPM/Matriculation/Diploma        |                            |              |                  |         |
| First degree                          |                            |              |                  |         |
| Second degree and third degree        |                            |              |                  |         |
| No formal education                   |                            |              |                  |         |
| Employment status              |                            |              |                  |         |

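### H1 and H2 assert baseline sameness, as do their nulls, and the difference tests planned for H1 (and implied for H2) cannot show it

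*Combined protocol and SAP*

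**What the plan says.** Section 1.6 lists four hypothesis pairs. H1 says that the sociodemographic, socioeconomic, working experience and "training attendance characteristics of the intervention and control groups would be the same"; its null H01 is "There is no significant differences in the sociodemographic, socioeconomic, working experience, and training attendance characteristics of the intervention and control groups". H2 is "The KAP on occupational safety and health at food premises of the intervention and control groups at the baseline would be the same"; its null H02 is "There is no significant differences in the KAP on occupational safety and health at food premises of the intervention and control groups at the baseline". H3/H03 and H4/H04, by contrast, set an effect against no effect.

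The Result paragraph of the Executive Summary repeats the expectation: baseline characteristics are "hypothesized to show no difference in between group".

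In section 4.1, Table A is headed "Baseline comparison of sociodemographic, socioeconomic, working experience, and training attendance characteristics between-group" and has columns for a statistical test and a p-value. Table B gives Mann-Whitney p-values for three social cognitive theory (SCT) construct scores and includes a baseline column. Section 3.10 names chi-square for pairs of categorical variables, without mentioning clustering. It says that alpha "will be set at 0.05" and adds: "A p-value of less than 0.05 pertained to the decision rule".

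No equivalence margin appears anywhere. Objective 1 in section 1.5.2 asks only for a description of baseline.

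**The concern.** A research hypothesis has to be something that its null denies. H1 and H2 agree with their nulls, and neither pair contains an alternative of difference. As written, two of the four stated hypotheses cannot be answered.

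The implied decision rule does not help. If p is above 0.05, the arms will be reported as the same, which a difference test cannot establish. If p is below 0.05, the randomisation will appear to have failed, although some small p-values are expected among many tests when nothing is wrong. What is at stake is an unsound conclusion about comparability, in either direction.

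**Working it through.** The plan gives no figure of its own on this point, so there is none to reproduce.

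**Inputs**
- Alpha 0.05 per test (section 3.10). Sidedness is not stated; two-sided is assumed.
- H1 tests: Table A has 11 characteristics (age, gender, ethnicity, education, employment status, individual income, household income, previous working experience, length of experience, previous training, typhoid injection). H1 does not cover typhoid injection, so the count is 10 or 11.
- H2 tests: 3 (knowledge, attitude, practice). This is an assumption, since no baseline KAP test is specified.
- Sample size: 139 (Executive Summary) or 240 (section 3.6). With 1:1 allocation (section 3.5) that is 69.5 or 120 per arm.
- Cluster size 12 (section 3.6). No intracluster correlation (ICC) is given, so 0.01 to 0.10 is assumed.

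**1. Can a non-significant test show sameness?** Normal approximation for a true difference of d SD, ignoring clustering: power = Φ(d·√(n/2) − 1.96), with n per arm.
- N=139, d=0.3: 0.3·√34.75 − 1.96 = −0.19; power 0.424, missed 58%.
- N=240, d=0.3: 0.3·√60 − 1.96 = 0.36; power 0.642, missed 36%.
- d=0.2: missed 78% (N=139) and 66% (N=240).

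With ICC 0.05 the design effect is 1 + 11·0.05 = 1.55. Dividing n by it, 0.3 SD is missed in about 70% and 54% of trials.

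A proper equivalence test (two one-sided 5% tests, true difference zero, no clustering) has power 2Φ(margin/√(2/n) − 1.645) − 1, or zero where that is negative. For a margin of 0.2 SD this is 0 at either size. For 0.3 SD it is 10% at N=139 and 50% at N=240.

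**2. How often would some p-value fall below 0.05 with no true imbalance?** For k independent tests without clustering, the chance is 1 − 0.95^k.

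| Tests | k | Chance of at least one p<0.05 |
|---|---|---|
| H2 only | 3 | 14.3% |
| H1 only | 10-11 | 40.1%-43.1% |
| H1 and H2 | 13-14 | 48.7%-51.2% |
| plus three Table B baseline tests | 17 | 58.2% |

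**3. How far do the assumptions move this?**
- Correlated tests: with 14 tests and a common correlation of 0.1, 0.2, 0.3 or 0.5, simulation gives 50%, 48%, 44% or 35%.
- Clustering ignored: the per-test error is 2·(1 − Φ(1.96/√DEFF)), with DEFF = 1 + 11·ICC. For ICC 0.01, 0.02, 0.05 and 0.10 it is 6.3%, 7.6%, 11.5% and 17.6%. Over 14 otherwise independent tests the chance becomes 60%, 67%, 82% and 93%.

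**The case against.** The best defence is that H1 and H2 are descriptive statements in hypothesis form. Objective 1 already says to describe. The primary outcomes and H3/H4 do not depend on them, and the plan attaches no action to any baseline p-value. Most of this stands, and it limits the consequences. It does not make the two pairs answerable, nor does it explain the test and p-value columns.

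Several stronger readings are tempting, but the document does not support them.

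- *Baseline significance will choose the covariates, leaving imbalances unadjusted.* No section says so. Section 3.6.2 names covariates, section 3.10 enters them in the mixed model without a significance screen, and objective 4 promises covariate control. The two lists differ: employment status and household income are in 3.10 but not among the covariates in 3.6.2. That leaves room for data-driven choice, which is a risk and not a stated rule.
- *H2 is to be tested.* Table A has no KAP row, and Table B covers SCT constructs. The inference rests on the wording of H02 and the general 0.05 rule.
- *False alarms will occur about half the time.* That figure pools H1 with three inferred KAP tests and assumes independence and no clustering.
- *The number of schools is small.* Section 3.5 does not say how many schools will be chosen, and section 3.6 speaks of 20 clusters.

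Nor need every small p-value be a false alarm. Section 3.5 describes assigning schools and then inviting attendees. If recruitment follows allocation, baseline differences may be real. That is a reason to describe balance carefully and adjust by a fixed plan; it does not rescue the p-value rule.

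**Conclusion.** The point holds. H1 and H2 cannot be distinguished from their nulls, and that needs no assumption. H1 is tied to difference tests by Table A and section 3.10; for H2 the tie is inferred.

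The test fails in both directions. It misses a 0.3 SD imbalance in 58% (N=139) or 36% (N=240) of trials before any design effect. With no imbalance it gives at least one p<0.05 in about 40-43% of trials for H1 alone, or 49-51% if three KAP tests are added. The latter figures assume independence and no clustering, so they are reference values within a wide range.

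A reader might infer that the treatment comparison is compromised. It is not: the H3 and H4 effect estimates are not invalidated by this defect. The correction is still worth making, because two stated hypotheses would otherwise end in an unsound conclusion and the repair costs little.

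**What to change.** 1. Delete H1/H01 and H2/H02 from section 1.6, and the matching sentence in the Result paragraph of the Executive Summary.
2. Remove the test and p-value columns from Table A and the baseline-column p-values from Table B.
3. Report baseline characteristics and the three KAP scores by arm, with standardised differences and the number of schools. This is what objective 1 asks for.
4. State one fixed covariate list for the KAP models, reconciling sections 3.6.2 and 3.10 on employment status and household income. Say that it applies whatever the baseline comparison shows.
5. Handle each baseline KAP score in one way only: either as a covariate, with post-training and one-month scores as outcomes, or as a baseline outcome level constrained equal across arms. The choice must be explicit because section 3.10 treats the baseline response as a random intercept and Table F, the only model table shown (for self-efficacy), has baseline as a level of time. Baseline should not be both outcome and predictor.

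**Cost:** items 1 to 3 are wording and table layout, plus a sentence for readers who expect baseline p-values. Items 4 and 5 need a small respecification of the model. No new data are needed.
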